## Study Intervention/Investigational Agent

No Drug or Device is being used for this intervention.

Primary intervention.

The intervention is messaging to hospitalists via email every 2 months (bi-monthly) that contains peer comparison data of the previous 2 months and antibiotic prescribing educational content. Draft content of this message is submitted.

The detail of the content is still to be developed, but may include a relative rank in prescribing metrics, with blinding to specific Peers' identity, with department wide and facility specific goals highlighted. Those in the lowest prescribing quartile will earn the designation of "Top Performer". The usual care arm will be an educational email about simple steps to improve antibiotic prescribing sent bimonthly to all hospitalists.

Secondary Intervention (if needed).

An interim analysis will occur at the facility-level after three quarters (9 months) of intervention data to determine if high prescribers (i.e., SAR above 1.25, or 25% higher than predicted) continue to prescribe high in more than half of the intervention bimonthly prescribing periods. This would be interpreted as a lack of effect to the email-based intervention, and a secondary intervention would be offered to all high prescribers consisting of bi-monthly check in with the stewardship lead (either infectious disease pharmacist or medical director of stewardship) at each facility to provide an open forum for questions and answers about the data and any clinical practices.

## Procedures Involved

Design. We will employ a quasi-experimental before-after study design, using a stepped wedge approach with 4 hospitals. Study participants will include all 147 full-time hospitalists. The intervention will be rolled out sequentially to all 4 hospitals in 3-month intervals. The intervention will last 18 months at all 4 sites.

Figure - Enrollment – facilities (EHC Entity) will be randomized to order of implementation roll out of intervention (INT), or continue baseline (BSLINE) usual care. Interim analysis (IA) would occur after 3 quarters of intervention to assess need for secondary intervention.

| EHC Entity | 18 months retrospective | QTR3   | QTR4   | QTR1   | QTR2   | QTR3   | QTR4   | QTR1  | QTR2-3 |
|------------|-------------------------|--------|--------|--------|--------|--------|--------|-------|--------|
| First      | BSLINE                  | INT    | INT    | INT    | IA+INT | INT    | INT    | INT   | INT    |
| Second     | BSLINE                  | BSLINE | INT    | INT    | INT    | IA+INT | INT    | INT   | INT    |
| Third      | BSLINE                  | BSLINE | BSLINE | INT    | INT    | INT    | IA+INT | INT   | INT    |
| Fourth     | BSLINE                  | BSLINE | BSLINE | BSLINE | INT    | INT    | INT    | IA+NT | INT    |

## Analysis Plan and Outcomes.

Primary outcome is the provider-specific SAR, separately for each antibiotic grouping. Secondary outcomes include CD, readmission (< 30 days of discharge), length of stay. Changes in 2-month SAR will be estimated using an interrupted time series analysis, evaluating changes in each antibiotic grouping separately, analysis will consider hospital fixed effects. Secondary outcomes will be analyzed at the patient level among all billed encounters using logistic or negative binomial regressions. Inclusion of provider and quarter-year fixed effects will control for time-invariant provider and site characteristics and secular time trends (e.g., seasonal patient mix) and establish a difference-in-difference framework. This approach will estimate the within-provider change in patient outcomes, pre- and post-intervention. We will control for patient (e.g., sex, age, Comorbidity Index) mix, time-variant provider (e.g., census) factors.

Data Sources: The primary source of data will be the EH Clinical Data Warehouse (CDW), a repository that integrates data from multiple clinical applications within EHC and has flexibility to create customized, research-specific metrics. Outcomes for Aim 2 will also be calculated from data elements within the EH CDW (i.e., re-admissions, length of stay.)

Provider-specific SARs. Data elements will be aggregated into 2-month intervals for each of the 147 hospitalists across each hospital. Billed Days of Therapy (bDOT) and billed patient-days (bPD) derived for each antimicrobial group will be limited to the eligible dates of each patient encounter to dates billed by a hospitalist (bPD). For each period, a SAR will be determined from provider specific bDOT calculated along with predicted DOT using preliminary regression models. Regression models will be created from analyzing summary provider specific data and providers' encounter data for each 2-month period of the baseline period. Encounter summary data will be aggregate number of encounters billed by

each provider, and the % of those billed encounters in which the patient had each of the listed comorbid conditions, resulting in a summary observation without any patient PHI (i.e., data will be at the provider level, with no. and percent of encounters with each condition, and no. of DOT for all encounter in aggregate). Patient comorbidities include age, renal disease, neurologic condition, heart failure, sepsis, urinary tract infection, pneumonia, COVID-19. SAR data will be analyzed using visualization software (flexdashboard for R) to create ranking visualization and tabular reports to identify high and low risk adjusted prescribers.

Patient safety. HMS monitors re-admission rates and LOS as routine quality indicators for each provider. Monthly values will be monitored by study team on a semi-annual basis to identify potential adverse effects among HMS patients.

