## 2. Intervention

The intervention will comprise two components: (1) a one-time educational session on antibiotic de-escalation and (2) bimonthly email feedback reports. Educational sessions, led by facility stewardship leads, will focus on evidence-based recommendations for presumed pneumonia and urosepsis, including indications for empiric anti-pseudomonal coverage and use of the hospital's antibiotic prescribing assistance tool. Feedback reports will reinforce these indications and will provide a link to the tool.

Provider-specific feedback reports will use observed-to-expected ratios (OERs), derived in part from EPIC Clarity System clinical and billing data. Generalized linear models will be used to generate OERs, adjusted for the proportions of patients with sepsis, end-stage renal disease, and urinary tract infections. These risk adjustments will be based on a prior study identifying factors consistently associated with broad-spectrum hospital-onset (BS-HO) antibiotic prescribing (Onwubiko et al. 2024).

Bimonthly, the stewardship research team will automatically email private PDF reports to each provider. Report content and formatting will be informed by CP-FIT's key feedback elements and will be assessed through cognitive interviews with 13 providers conducted during the development phase, with corrective changes to be implemented based on structured interview questions.

One week after the third prescribing report is sequentially sent (six months after intervention initiation), the antibiotic stewardship team will email a single-question Microsoft Form survey to providers, seeking confirmation of whether they viewed the previous reports. Non-responders will receive email reminders from the hospital medicine faculty liaison, who will then personally follow up with remaining non-responders to encourage completion.

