#### **5. Study Measures and Outcomes**

Data from January 2023 to December 2024 will be extracted for inpatients at all hospitals with Hospital Medicine Services. For each hospitalist, billing data will be used to identify patient encounters and to calculate billed patient-days (bPD). Antibiotic prescribing data from electronic medication administration records (eMAR) will capture days of antibiotic therapy (DOT) for NHSN-defined broad-spectrum hospital-onset (BS-HO) agents per bPD.

Patient characteristics linked to each encounter will include age, microbiology results (e.g., bacteremia), ICD-10–based antibiotic indications (e.g., pneumonia, COVID-19, sepsis, urinary tract infection), and comorbidities, enabling calculation of Elixhauser comorbidity indices. Generalized linear models will be used to generate provider-level observed-to-expected ratios (OERs). In each model, bPD will remain continuous, while other predictors will be categorized by quintiles based on their relationship with DOT. Based on input from Hospital Medicine Services leadership and focus groups, hospital-specific models will be used to calculate OERs in order to maximize provider credibility of the metric.

The primary outcome will be the observed provider-specific antibiotic prescribing rate, defined as billed DOT of BS-HO antibiotics per 1,000 billed patient-days. This measure alone will not be risk adjusted; however, patient- and provider-level characteristics will be adjusted for and included as covariates in the regression model described below. For illustrative (descriptive) purposes, risk-adjusted provider-specific OERs will also be estimated, with point estimates (means) and variance plotted over time by facility. OERs will not be modeled directly as regression outcomes.

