## **7. Statistical Analysis**

**For the primary outcome analysis,** a generalized linear mixed-effects model with a negative binomial distribution and log link will be used to evaluate the effect of the intervention on antibiotic prescribing rates over time. The observed DOT will be modeled as a function of provider receipt of feedback reports, time (bimonthly period) to account for secular trends and time-varying confounding, and a random facility effect to account for clustering of providers within hospitals. A random intercept for each provider nested within facility will be included to account for correlation among repeated observations and the hierarchical data structure. The intra-cluster correlation coefficient (ICC) will be estimated to quantify the proportion of total variance attributable to between-cluster differences. Models will adjust for patient-mix characteristics as covariates.

Sensitivity analyses of the primary outcome will be conducted among the subset of providers who indicate that they received and reviewed the feedback reports, to account for potential implementation bias.

**Secondary outcomes will be analyzed at the patient level** among all patients receiving care from hospital medicine services and discharged with ICD-10 codes for pneumonia or urinary tract infection, as this group is expected to be most vulnerable to changes in antibiotic de-escalation practices. Safety outcomes will be analyzed using generalized mixed-effects logistic regression models to evaluate intervention effects over time, accounting for repeated hospitalizations within patients and clustering by facility. Covariates will include time (to account for seasonality) and patient-level indicators (COVID-19, influenza, Elixhauser comorbidity index, and sepsis). All analyses will be performed using R Statistical Software (version 4.2.0; R Core Team, 2021).

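### Same-window sepsis, UTI and pneumonia shares, very likely covariates for the primary estimate, could move at crossover, and no planned analysis would show whether they did

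*Combined protocol and SAP*

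**What the plan says.** **Protocol, Analysis Plan and Outcomes.** "Primary outcome is the provider-specific SAR, separately for each antibiotic grouping". On its construction: "For each period, a SAR will be determined from provider specific bDOT calculated along with predicted DOT using preliminary regression models". The inputs are provider-level summaries, including "the % of those billed encounters in which the patient had each of the listed comorbid conditions", and the list of conditions reads "Patient comorbidities include age, renal disease, neurologic condition, heart failure, sepsis, urinary tract infection, pneumonia, COVID-19". The prediction models are fitted on baseline data, but the case-mix values fed into them belong to the window being scored.

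**SAP section 5.** The primary outcome is now the observed rate of broad-spectrum hospital-onset (BS-HO) days of therapy (DOT) per 1,000 billed patient-days. Observed-to-expected ratios (OERs) are kept for feedback and description and are not modelled as outcomes. Of the rate, it says "patient- and provider-level characteristics will be adjusted for and included as covariates in the regression model described below". Pneumonia, COVID-19, sepsis and UTI, identified by ICD-10 code, are among the characteristics linked to each encounter.

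**SAP section 7.** "Models will adjust for patient-mix characteristics as covariates". No covariate is named for the primary model. The one sensitivity analysis of the primary outcome is restricted to providers who say they received and read their reports.

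**SAP section 2.** The educational sessions "will focus on evidence-based recommendations for presumed pneumonia and urosepsis". The feedback OER is adjusted for the proportions of patients with sepsis, end-stage renal disease and UTI; pneumonia is not in that list.

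**The concern.** In an intervention window, an infection share is measured after crossover, and an infection diagnosis lies close to the decision to treat. Two responses to the intervention could move it:

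- Hospitalists stop diagnosing and treating doubtful infections. Part of the real fall in DOT then passes through the share, and adjusting for the share removes that part.
- Hospitalists document sepsis or UTI more fully once they see a ratio whose denominator depends on them. Expected prescribing rises, and the adjusted estimate falls with no change in antibiotic use.

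Two features of the plan do not protect against this. Baseline-fitted SAR coefficients do not help, because the covariate values still come from the intervention window. The common period effect does not help, because the shift would follow each hospital's own crossover. What is at stake is whether the reported rate ratio can be read as a change in prescribing.

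**Working it through.** **1. The plan's own benchmark.** The Study Summary names a 10% reduction, with 80% power for an effect size of 0.9 to 1.1 in 147 providers. It gives no ICC or SD, so the power figure can be neither confirmed nor refuted; this point does not depend on it. The 10% serves only as a yardstick. The documents give no coded share, no prescribing ratio by code and no expected coding shift, so all three are assumed below and shown as ranges.

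**2. Algebra for an observed-to-expected measure.** Let p be the share of encounters coded with a targeted infection, and RR the ratio of DOT in coded to uncoded encounters. Expected DOT is proportional to 1 + p(RR − 1).

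Middle case, p = 0.30 and RR = 3:
- Baseline: 1 + 0.30 × 2 = 1.60.
- Share down 10% to 0.27: 1.54 / 1.60 = 0.9625. A real fall of 3.8% acting through the share is hidden.
- Share up 10% to 0.33, prescribing unchanged: 1.60 / 1.66 = 0.964. A false fall of 3.6% appears.
- To hide a full 10% reduction: p = (0.9 × 1.60 − 1) / 2 = 0.22, a 27% relative fall.
- To create a false 10% reduction: p = (1.60 / 0.9 − 1) / 2 = 0.389, a 30% relative rise.

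| RR, p | Hidden if p falls 10% | False fall if p rises 10% | Fall in p that hides 10% | Rise in p that fakes 10% |
|---|---|---|---|---|
| 2, 0.15 | 1.3% | 1.3% | 77% | 85% |
| 3, 0.30 | 3.8% | 3.6% | 27% | 30% |
| 5, 0.45 | 6.4% | 6.0% | 16% | 17% |

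**3. Simulation of a SAP-type rate model.** Inputs: 125 hospitalists in four hospitals (40, 35, 30 and 20, within the SAP's 15 to 40), 12 two-month windows, crossovers at windows 4 to 7 as for Hospitals A to D in SAP Figure 1, p = 0.30, RR = 3. A negative binomial model with hospital and period effects was fitted with and without the same-window share, 60 trials per scenario. The true value in row 1 is (1 + 0.30 × 0.85 × 2) / 1.60 = 0.944; row 2 multiplies it by 0.95.

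| Scenario | True rate ratio | Without share | With share |
|---|---|---|---|
| Real fall through 15% fewer coded infections | 0.944 | 0.947 | 1.001 |
| Same, plus direct effect 0.95 | 0.897 | 0.897 | 0.949 |
| Coding up 15%, prescribing unchanged | 1.000 | 1.011 | 0.960 |
| Direct 10% effect, no coding change | 0.900 | 0.891 | 0.891 |

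The last row, where neither fit should err, shows simulation noise of about 0.01.

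**4. A second simulation with separate codes.** It uses provider and window effects, and 437,303 / 116 / 18 = 209 billed patient-days per provider-window from the protocol's preliminary data. Assumed: 5 patient-days per encounter; UTI 20%, sepsis 15% and pneumonia 15% of encounters. There were 40 runs per scenario, with Monte Carlo SE about 0.008.

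| Scenario | True | Without infection terms | With them |
|---|---|---|---|
| UTI diagnoses down 20%, RR 2 | 0.976 | 0.967 | 0.991 |
| UTI diagnoses down 30%, RR 3 | 0.935 | 0.935 | 1.000 |
| Sepsis codes up 2 points, RR 2 | 1.000 | 1.008 | 0.998 |
| Sepsis codes up 3 points, RR 3 | 1.000 | 1.012 | 0.980 |
| Sepsis codes up 5 points, RR 4 | 1.000 | 1.000 | 0.935 |
| Direct 10% effect, no coding change | 0.900 | 0.894 | 0.892 |

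Neither simulation fits the SAP's nested random-effects model exactly, and neither includes a real hospital-specific change in case mix.

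**The case against.** **The SAP does not say that these codes are in the primary model.** The explicit list belongs to the protocol's SAR. A reader might infer that the primary model is known to adjust for all three infections; section 7 names none, and pneumonia is absent even from the feedback ratio. This stands. What the documents support is that the codes are very likely covariates and that nothing excludes them.

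**The education concerns which drug to give once an infection is presumed, not whether to diagnose or code it.** This also stands, and under that mechanism both simulations show no harm from adjustment. A reader might infer that the estimate is biased as planned; that requires a shift in diagnosis or coding, which the documents neither report nor rule out.

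**The incentive to code more is thinly documented.** The protocol says "Those in the lowest prescribing quartile will earn the designation of" top performer, without tying this to the ratio, and describes the content as still in development. The SAP mentions no such award. A reward for up-coding should therefore not be read into the plan. What remains is that providers are shown a ratio adjusted for sepsis and UTI, and that the protocol defines high prescribers by a SAR above 1.25.

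**The size can be overstated.** In the two smaller sepsis scenarios the gaps between fits are 1.0% and 3.2% (0.998 / 1.008 and 0.980 / 1.012). Against the truth the errors are 0.2%, within Monte Carlo error, and 2.0%. A single trial's standard error in that set-up is about 0.05, so only the largest shifts exceed it.

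**Adjustment has a purpose.** With four hospitals, a common period effect cannot absorb a real change in infection mix at one of them, and the protocol endpoint is meant to account for patient mix. It does not follow that the infection shares must leave the primary model: the cost of dropping them was not tested.

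**Conclusion.** The point holds as a gap in specification and in safeguards, not as a demonstrated bias. If coded shares move at crossover, the adjusted rate ratio no longer measures the total effect on prescribing, and the direction of error cannot be known in advance. Modest shifts matter by a few percent. Hiding or faking the whole 10% target needs a relative shift of roughly 16% to 85%, depending on direction, prevalence and prescribing ratio. All of these sizes rest on assumed inputs. The firm part is that the covariate list is open and the plan contains no analysis that could separate a change in drug choice from a change in diagnosis or coding. That is worth correcting because it affects what the trial can conclude and costs little.

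**What to change.** In SAP section 7:

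1. Name the primary-model covariates, and mark those the intervention could affect: same-window sepsis, UTI and pneumonia shares.
2. Pre-specify a companion fit of the primary model without those shares, or with them fixed at each provider's pre-crossover values, and report it beside the adjusted estimate. Which fit is labelled primary is for the sponsor to decide.
3. Fit the same stepped-wedge model with each coded share as the outcome. If a share moves at crossover, interpret the adjusted estimate as excluding that pathway. With four hospitals, a null result would not rule out a modest shift, so report the interval.
4. If the protocol's SAR endpoint is kept, apply the same check to it. The primary outcome differs between protocol and SAP and should be reconciled in any case.

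The feedback ratio itself need not change. The cost is SAP wording and a few extra fits on data already collected. The companion fit gives less control of real case-mix shifts, which is why both estimates should be shown.

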## Data Specimen Banking

No plans for data or specimen banking for future use.

## Sharing of Results with Participants

HMS providers will be receiving data on prescribing as part of the intervention, results of the impact of this QI will be shared with HMS and all providers through Departmental meetings at the tail end of the study period. There are no plans to share results with patients cared for on the HMS service.

## Study Timelines

All HMS providers will be expected to participate in this QI Activity as per Department prerogative (Department chair is not a collaborator on this project, but has expressed interest in this QI and fully supportive)

- Spring 2022 - Approvals and Socialization of the QI initiative with HMS
- Spring-summer 2022 Baseline analysis and regression modeling completion
- Summer 2022 - Creation of bimonthly feedback report
- October 2022 - Roll out of intervention
- October 2023 - Data and safety monitoring, interim evaluation with HMS leadership
- March-Summer 2024 - Final analysis and internal discussions on maintaining intervention or modification
- January 2025 - Publication of results

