| Sample Size                                | Including 147 HMS providers, accounting for cluster effect we should be able to detect a large effect size (.9 to 1.1) with 80% statistical power. This translates to reductions in prescribing rates of 10% during intervention period from baseline period. |
| Study Duration for individual participants | October 2022 – December 2024                                                                                                                                                                                                                                  |

|                                                  |                                                                                                                                                                  |
|--------------------------------------------------|------------------------------------------------------------------------------------------------------------------------------------------------------------------|
| Study Specific Abbreviations/ Definitions | Hospital Medicine Service (HMS)
Standardized Antibiotic Prescribing Ratio (SAR)
C. difficile infection (CDI)
Days of Therapy (DOT)
Patient-days (PD) |
| Funding Source (if any)                   | Centers for Disease Control and Prevention                                                                                                                       |

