### 3. Study Design

We plan to use a Randomized Step Wedge Cluster Design (R-SWCD) to evaluate the effect of the peer comparison feedback report on antibiotic prescribing (BS-HO group). The study will be conducted in 4 hospitals (clusters) in Atlanta, Georgia. Of note, pending discussion with Hospital Medicine Leadership, the intervention may also be rolled out at an additional hospital, although lack of retrospective data would not allow inclusion of this facility in the full analysis. Hospitals will begin in the control condition and end in the intervention condition, wherein, all hospitals will receive the intervention and cross over to the intervention arm in a random order (Figure 1). Randomization will occur at the hospital level rather than at the provider level to avoid contamination and spillover effects. Providers within a hospital are not fully independent of each other, groups tend to form because of certain selection factors, and so providers tend to be more similar to each other with respect to potential confounders.

Outcomes linked to the same provider will be assessed repeatedly on a bi-monthly bases in each hospital over a two-year time period (2023-2024). Hospitals will cross-over to the intervention arm sequentially, resulting in 4 steps with an equal step length of 2 months. Following a baseline period (January 1 - June 30, 2023), the first cluster will begin the intervention on July 1, 2023. The final cluster will transition by March 1, 2024, with intervention continuing through December 31, 2024 in all hospitals.

A step wedge design, which involves the randomized and sequential roll out of the intervention to hospitals over time was chosen as it can model and adjust for any underlying temporal trends and results in all hospitals receiving the intervention **which is desirable from a healthcare quality improvement and antimicrobial stewardship perspective**. Randomization of the order of implementation reduces confounding from baseline cluster-level factors. Lastly, gradual roll out of the intervention will allow us to identify and address any implementation bottlenecks.

**Figure 1.** Stepped-Wedge interventional study design. Abbreviations: E, educational session; PF, Provider Feedback. Grey boxes reflect intervention periods with bi-monthly PF reports.

|            | 2023       |        |        |        | 2024   |        |               |
|------------|------------|--------|--------|--------|--------|--------|---------------|

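### The protocol dates the final analysis, and talks on modifying the intervention, to March-Summer 2024, but its own roll-out and the SAP run the intervention to December 2024

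*Combined protocol and SAP*

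**What the plan says.** Study Timelines in the protocol gives the start as "October 2022 - Roll out of intervention" and then lists "March-Summer 2024 - Final analysis and internal discussions on maintaining intervention or modification". Publication follows in January 2025. This is the only date for a final analysis in either document.

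Other parts of the protocol imply a later end. Procedures Involved states "The intervention will be rolled out sequentially to all 4 hospitals in 3-month intervals" and "The intervention will last 18 months at all 4 sites". The Study Summary gives the duration for individual participants as "October 2022 – December 2024".

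SAP section 3 (Study Design) moves the start: "the first cluster will begin the intervention on July 1, 2023". It describes the trial "with intervention continuing through December 31, 2024 in all hospitals". SAP section 5 (Study Measures and Outcomes) extracts data from January 2023 to December 2024. The SAP names no date for the final analysis or for data lock.

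On disclosure, the protocol's Sharing of Results with Participants says "results of the impact of this QI will be shared with HMS and all providers through Departmental meetings at the tail end of the study". Two interim looks are planned in the protocol: a facility-level look after nine months of intervention, which can trigger a secondary intervention (Study Intervention), and an October 2023 evaluation with service leadership (Study Timelines).

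**The concern.** The participants are the hospitalists, the intervention is feedback on their prescribing, and the outcome is that same prescribing. When the effect is estimated, who learns of it and whether the reports then change can all alter what later two-month windows measure.

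The timeline puts the final analysis before the end of exposure and pairs it with discussion of modifying the intervention. Three things follow if it is kept:

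- The result labelled final would leave out planned exposed time, chiefly the longer exposures.
- If providers heard the result, or the reports were altered because of it, later windows would no longer measure the planned intervention.
- A further analysis of data to December 2024 would be a second look at the primary outcome, which neither document describes.

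No passage withholds effect estimates from providers, or holds the reports fixed, until data collection ends.

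**Working it through.** **1. Reproduce the protocol's end date.** Inputs: first start October 2022 (Study Timelines); four hospitals, three-month steps, 18 months (Procedures Involved).

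- Starts: October 2022, January 2023, April 2023, July 2023.
- Fourth hospital: July 2023 + 18 months = end of December 2024. From October 2022 that is 3 × 3 + 18 = 27 months, which matches the stated duration.
- The roll-out table agrees on length: 9, 8, 7 and 6 intervention quarters, or 27 + 24 + 21 + 18 = 90 hospital-months.

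**2. Gap to the scheduled analysis.** From 1 March 2024 to 31 December 2024 is 10 months. From 31 August 2024 (taken as the end of summer) it is 4 months.

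**3. Exposure accrued under the protocol's roll-out.** Sum over hospitals of (cut-off − start):

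| Cut-off | Months by hospital | Total | Share of 90 |
|---|---|---|---|
| 1 March 2024 | 17, 14, 11, 8 | 50 | 56% |
| 31 August 2024 | 23, 20, 17, 14 | 74 | 82% |

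**4. Interim look at the fourth hospital.** July 2023 + 9 months = about April 2024, after a final analysis opening in March 2024.

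**5. Other readings of the protocol.**

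- Suppose the table's labels are calendar quarters starting with the third quarter of 2022 (an assumption that does not fit the October 2022 start). The intervention then ends on 30 September 2024, a gap of 7 to 1 months. Accrual is 20 + 17 + 14 + 11 = 62 of 90 (69%) on 1 March and 26 + 23 + 20 + 17 = 86 of 90 (96%) on 31 August. The fourth hospital's interim look moves to about January 2024, so step 4 no longer applies.
- Suppose instead that each hospital stops at exactly 18 months. The total is 72, with 50 of 72 (69%) and 18 + 18 + 17 + 14 = 67 of 72 (93%). The last hospital still ends in December 2024. On this reading the first hospital finishes at the end of March 2024, which may be where the March date came from (inference).

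On every reading the final analysis opens before the intervention ends.

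**6. SAP roll-out, for comparison only.** No document pairs these starts with a 2024 final analysis.

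- Figure 1 starts (July, September, November 2023, January 2024): 20 of 60 hospital-months (33%) by 1 March 2024 and 44 of 60 (73%) by 31 August.
- Last start on 1 March 2024, as in the SAP text: 18 of 58 (31%), none from the last hospital, and 42 of 58 (72%).

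**7. Publication line.** For a patient discharged on 31 December 2024, 30-day readmission runs to 30 January 2025. *C. difficile* follow-up of eight weeks (SAP section 6) runs to 25 February 2025. January 2025 publication cannot include either in full.

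**8. What the missing months are worth in precision.** Assumptions: equal-sized hospitals, categorical periods, a constant effect, and a random hospital intercept with a hospital-to-residual variance ratio r from 0.1 to 10,000. The variance is the treatment element of (Σ XᵀV⁻¹X)⁻¹ with V = I + rJ. Stopping at 1 March 2024 rather than December raises the standard error by about 1-2% (protocol roll-out), 2-8% (SAP Figure 1) or 2-12% (SAP text). At 31 August the increase is at most about 3%.

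**The case against.** The strongest reply is that the SAP governs the analysis and plans to use data through December 2024. Its first start is nine months after the protocol's, so the protocol calendar is simply out of date. Shifted by nine months, March-Summer 2024 becomes roughly December 2024 to mid-2025, close to where it should be. This is a fair guess at intent. But the SAP gives no analysis date to replace the protocol's, and the conflict exists inside the protocol before the SAP is considered.

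A reader might infer three stronger claims, and the documents support none of them.

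- That the trial plans to report on incomplete data. This follows only if the timeline is kept, and the SAP's extraction window says otherwise.
- That a change to the intervention is scheduled mid-measurement. The protocol speaks of internal discussions, gives no effective date for any change, and does not tie the sharing of results to March 2024.
- That 27% to 67% of exposed data would be lost. That range puts the protocol's analysis date on the SAP's Figure 1 roll-out, a combination no document plans.

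The share of months is also not the share of information. Apart from the SAP text's 1 March 2024 crossing, which falls exactly at the earlier cut-off, all omitted time comes after the last crossover, when no control hospital remains. Step 8 shows a small loss of precision for a constant effect. SAP section 7 names no exposure-duration term, so persistence of effect is not a specified primary target. This stands: lost power is not the main worry.

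Finally, a blanket ban on estimates reaching leadership would collide with the interim looks the protocol already plans. That also stands, and the fix allows for it.

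**Conclusion.** The point holds as an unreconciled timeline with consequences for conduct. The final-analysis date precedes the December 2024 end that the protocol implies and the SAP states, by 4 to 10 months if summer ends on 31 August. Followed under the protocol's October 2022 start and table lengths, it would capture 56% to 82% of planned intervention hospital-months.

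It is more than a clerical slip because this line sets when the trial concludes and couples that to modifying the intervention, while the disclosure section lets results reach the providers being measured. The bias is a possibility left open, not a planned event, and its size cannot be computed from the documents. The arithmetic is certain given those dates; what the sponsor intends for 2024 is not. The change should be made.

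**What to change.** - Reconcile the protocol's Study Summary, Procedures Involved and Study Timelines with SAP sections 3 and 5. Give one date for the data cut and final analysis, after 31 December 2024 plus the last outcome follow-up (30-day readmission and eight-week *C. difficile*, so not before late February 2025). Repeat it in the SAP.
- Move the January 2025 publication line accordingly.
- State that, apart from the interim looks already planned in the protocol (the nine-month facility look and the October 2023 evaluation), effect estimates are not shared with providers, and feedback reports are not modified on the basis of effect results, until data lock. Planned safety monitoring is unaffected.
- In Sharing of Results with Participants, replace the reference to the tail end of the study period with a time after data lock.
- Label any 2024 look at the effect as interim.

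The cost is a coordinated edit to several dates and a few sentences. The real downside is a later discussion of whether to maintain or modify the intervention, and later publication.
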